### Statistical methods

#### Data management and analysis software

Castor EDC software will be used for data management. This ICH-GCP compliant web-based software covers all aspects of data management, data collection, ADE/SAE reporting, randomization, patient surveys and monitoring in multi-center studies. Patients will receive an e-mail via Castor with a request to fill-in the questionnaires.

All data is gathered from study 1 and 2 for data collection and cleaning via direct entry in Castor EDC (electronic case report forms (eCRF)). The eCRF data in the Castor EDC are stored on an accredited data center hosting in the Netherlands (accreditations: ISO 27001:2013, ISO 9001 and NEN7510). Data can be retrieved from this data center at any point in time to perform the required statistical patient data analyses led by Antwerp University Hospital. Full audit trail is available to log every change to the trial’s data as well as which user made the change.

All statistical analyses will be performed in SAS version 9.4 or higher, R version 3.3.2 or higher, or SPSS 24.

### Statistical analyses

#### Analysis of the primary outcome

To answer the research question comparing the three treatment arms the research question is split up in three separate questions:
*Is there a difference between DIS and IBLA (≤4 weeks)?*

Results from study 1 will be used in a linear regression model with IKDC at 6 months as outcome and treatment, and IKDC at baseline as predictors. This linear regression model will allow correction for possible confounders like age, gender and working category.
*Is there a difference between IBLA (5–12 weeks) and conventional ACL reconstruction?*

Results from study 2 will be used in a linear regression model with IKDC at 6 months as outcome and treatment, and IKDC at baseline as predictors. This linear regression model will allow correction for possible confounders like age, gender and working category.
*Is there a difference between DIS and conventional ACL reconstruction?*

Results from study 1 and study 2 will be compared using a linear regression model with IKDC at 6 months as outcome and treatment, and IKDC at baseline as predictors. As this is a non-randomized comparison this model will correct for possible confounders like age, gender and working category.

For the primary analysis all patients that didn’t have a repairable, proximal ACL rupture will be excluded from the analysis (exploratory group). Patients with a failure or re-surgery will be included in the primary analysis.

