**Methods:**

Subjects, aged 18–50 years, with a proximal, primary and repairable ACL rupture will be included. DIS is preferably performed within 4 weeks post-rupture, IBLA within 12 weeks and reconstruction after 4 weeks post-rupture. Patients are included in study 1 if they present within 0–4 weeks post-rupture and surgery is feasible within 4 weeks post-rupture. Patients of study 1 will be randomized to either DIS or IBLA. Patients are included in study 2 if they present after 4 weeks post-rupture and surgery is feasible between 5 and 12 weeks post-rupture. Patients of study 2 will be randomized to either IBLA or reconstruction. A total of 96 patients will be included, with 48 patients per study and 24 patients per study arm. Patients will be followed-up for 2 years. The primary outcome is change from baseline (pre-rupture) in International Knee Documentation Committee score to 6 months post-operatively. The main secondary outcomes are the EQ-5D-5 L, Tegner score, Lysholm score, Lachman test, isokinetic and proprioceptive measurements, magnetic resonance imaging outcome, return to work and sports, and re-rupture/failure rates. The statistical analysis will be based on the intention-to-treat principle. The economic impact of the surgery techniques will be evaluated by the cost-utility analysis. The LIBRƎ study is to be conducted between 2018 and 2022.

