### Study procedures

Table 1 gives an overview of the clinical and radiological evaluations the patient will encounter in both centers following written informed consent. The physiotherapy will be performed by the patient’s physiotherapist according to the study-specific rehabilitation protocol. This physiotherapy protocol is based on five phases. Proceeding to the next phase depends on the patients rehabilitation progress and not on the post-operative time.

**Table 1 Tab1:** Pre-, intra- and post-operative clinical and radiological evaluations

Timepoint	Clinical and radiological evaluations
Pre-operative	Pre-rupture: Tegner score, Lysholm score and IKDC score Post-rupture: VAS pain, knee function, Lachman test, EQ-5D-5 L, isokinetic and proprioceptive measurement, and MRI
Intra-operative	Knee function, pivot shift test, surgery time and complications
Post-Operative	
Day 1	VAS pain, return to work rupture-surgery interval, EQ-5D-5 L and complications
Week 2	VAS pain, return to work, knee function, EQ-5D-5 L and complications
Week 6	VAS pain and satisfaction, mobilization with crutches, return to work, return to sports, knee function, Lachman test, EQ-5D-5 L, complications and X-ray knee
Week 13 (3 months)	VAS pain and satisfaction, mobilization with crutches, return to work, return to sports, knee function, Lachman test, EQ-5D-5 L, Tegner score, Lysholm score, IKDC score, complications, and isokinetic and proprioceptive measurement
Week 26 (6 months)	VAS pain and satisfaction, return to work, return to sports, knee function, Lachman test, EQ-5D-5 L, Tegner score, Lysholm score, IKDC score, complications, number of physiotherapy and orthopaedic surgeon consults, single leg and triple leg hop test, isokinetic and proprioceptive measurement, and MRI
Week 52 (1 year)	VAS pain and satisfaction, return to work, return to sports, knee function, Lachman test, EQ-5D-5 L, Tegner score, Lysholm score, IKDC score, complications, number of physiotherapy and orthopaedic surgeon consults, single leg and triple leg hop test, triple crossover hop and drop jump test, isokinetic and proprioceptive measurement, and MRI
Week 104 (2 years)	VAS pain and satisfaction, return to work, return to sports, knee function, Lachman test, EQ-5D-5 L, Tegner score, Lysholm score, IKDC score, complications, number of physiotherapy and orthopaedic surgeon consults, and MRI

*IKDC* International Knee Documentation Committee, *MRI* magnetic resonance imaging, *VAS* visual analogue scale

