### Sample size

The primary outcome is change in IKDC score from baseline (pre-rupture) to 6 months post-operatively. A difference in IKDC change score of 13 points between the treatment arms is considered clinically meaningful as described by Irrgang et al. and Collins et al. [46, 47]. In order to detect an effect of 13 IKDC points with 80% statistical power between any of the two treatment arms using an independent samples t-test in which alpha is 0.025 (alpha corrected for the fact that per study data set 2 tests will be performed), assuming a standard deviation of 13 on the change in IKDC score per arm (SD found in pilot study), we need 21 patients per arm. Taking into account a drop out of 10%, we need 24 patients per arm or 48 patients in total which have to be randomized.

In study 1, 24 patients per arm (DIS and IBLA) will be included and in study 2, 24 patients per arm (IBLA and ACL reconstruction) will be included. The total number of patients to be included is 96. We expect that 50% of the patients will be included in Antwerp University Hospital and 50% in University Hospital Brussels. We also expect that the total number of addressed patients will range from 96 to 106, since we expect that about 10% of the patients will not have a repairable, proximal ACL rupture. They will not be eligible (any more) after the intra-operative confirmation and these patients (exploratory group) will not contribute the number of 96 patients needed for inclusion.

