#### Analysis of the secondary outcomes

To evaluate robustness of the results a sensitivity analysis of the primary outcome will be done using different analysis sets.Analysis set without failures: patients that have a failure within the 6 months of follow-up are excluded from this analysisAnalysis set without re-surgeries: patients that have a re-surgery within the 6 months of follow-up are excluded from this analysisIn case we are not able to show superiority between the arms, we will consider non-inferiority between the arms. To this end we will choose 10 IKDC points as non-inferiority margin (see Hoogeslag et al. [25]). Non-inferiority will be considered in the different analysis sets and only be concluded if they give similar findings. The analysis sets considered here are intention-to-treat, the analysis set without failures and the analysis set without re-surgeries.As the IKDC scores are measured at many different time points during the patient’s follow-up we can compare the evolution over time between the treatment arms using a linear mixed model. Also here we will consider the effect of failure and re-surgery through inclusion and exclusion of the results after failure.Linear regression will be performed on the changes from baseline to 24 months in the continuous outcomes like VAS pain, VAS satisfaction, Tegner score, Lysholm score, EQ-5D-5 L, Lachman test, single leg and triple leg hop test, triple crossover hop and drop jump test, isokinetic and proprioceptive measurement and knee function. The evolution over time of these continuous outcomes will be compared between the different treatments using a linear mixed model.A survival analysis with log-rank test will be used to compare the time to return to work and time to return to sports between the different treatment arms. The time from the surgery until the patient is mobile without crutches will be analysed in the same way.The number of physiotherapy/orthopaedic surgeon consults will be compared between the different treatment arms using linear regression.The morphology and signal intensity of the ACL will be assessed with MRI and compared between the different treatments using a Chi-square test at the different time points.

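### The primary regression on the single 6-month IKDC, run as written, ignores the week-13 IKDC of patients who then drop out; a two-visit model or imputation would use it

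*Protocol article*

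**What the plan says.** All references are to the protocol article.

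- **Primary model (Analysis of the primary outcome).** For study 1: "Results from study 1 will be used in a linear regression model with IKDC at 6 months as outcome", with treatment and baseline IKDC as the predictors. Study 2 and the DIS versus reconstruction comparison have the same form. On who stays in: "Patients with a failure or re-surgery will be included in the primary analysis". Patients without a 6-month score are not mentioned.
- **Dropout (Sample size).** "Taking into account a drop out of 10%, we need 24 patients per arm or 48 patients in total which have to be randomized".
- **Principle (Abstract, Methods).** "The statistical analysis will be based on the intention-to-treat principle".
- **Data (Study procedures, Table 1).** The week-13 visit includes "Tegner score, Lysholm score, IKDC score, complications, and isokinetic and proprioceptive measurement". IKDC is repeated at weeks 26, 52 and 104.
- **Mixed model (Analysis of the secondary outcomes).** For the repeated IKDC scores, "we can compare the evolution over time between the treatment arms using a linear mixed model". This is a secondary analysis. The sensitivity sets for the primary outcome leave out patients with a failure or with a re-surgery.

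**The concern.** A regression on one post-operative score has no place for a patient who lacks that score. The only other IKDC value in the model is the pre-rupture one, which cannot reflect how the knee recovered after surgery. The week-13 score can, and it is the best available information on a patient who leaves between 3 and 6 months.

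If patients with poor early recovery leave more often in one arm than in the other, the remaining patients are selected differently and the contrast shifts. The sensitivity sets would not reveal this, because each of them has the same gap. The set labelled intention-to-treat, used for the fallback non-inferiority claim with its 10-point margin, has it too. Equal dropout is least assured in the DIS versus reconstruction comparison, which runs across the two studies and is not randomized.

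**Working it through.** **1. The plan's own figure.** Inputs from Sample size: difference 13, SD 13, alpha 0.025, power 80%. Sidedness is not stated; two-sided reproduces the figure. The two-sample t-test with standardized effect 13/13 = 1.0 gives n = 20.3, so 21 per arm. Allowing for dropout: 21/0.90 = 23.3, so 24 per arm. Both figures reproduce.

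**2. Power with observed cases only.** A 10% loss leaves 24 × 0.90 = 21.6 per arm. Power is 81.5% with 21 per arm, 82.7% with 21.6 and 87.0% with 24. The planned 80% is kept.

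**3. Bias if dropout depends on the week-13 score.** The documents give neither the correlation r between the 3- and 6-month scores nor any dropout pattern. I assume r = 0.5 to 0.7 and SD 13 at both visits. If selection on the week-13 score raises the mean of the remaining patients by k SDs, their 6-month mean rises by

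shift = r × k × 13.

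The bias in the contrast is the difference between the two arms' shifts.

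*Gradual selection.* Dropout is 10% overall, and the log-odds of leaving rise by 1 for each SD below the mean at week 13. Numerical integration gives k = 0.091, so k × 13 = 1.18.

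| Pattern | r = 0.5 | r = 0.7 |
|---|---|---|
| This mechanism in one arm, random 10% in the other | 0.59 | 0.83 |
| Opposite mechanisms in the two arms | 1.18 | 1.65 |
| Same mechanism in both arms | 0 | 0 |

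With a weaker slope of 0.75, k × 13 = 0.92. The one-sided bias is then 0.46 to 0.65 and the opposite-pattern bias 0.92 to 1.29.

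*Sharp selection.* The worst fraction p at week 13 leaves, so k = φ(z_p)/(1 − p). For p = 0.15, k × 13 = 3.57. For p = 0.05, k × 13 = 1.41. With 15% loss in one arm and 5% in the other, the bias is r × (3.57 − 1.41), or 1.1 to 1.5 points. A simulated true difference of 13 came out as 11.9 and 11.5. With 10% in both arms it stayed at 13.0. An extreme 20%/0% split gave 10.7 and 9.8.

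**4. The same data with the week-13 score used.** In the sharp-selection simulations the estimate was 13.0 in every pattern. In simulated trials of 24 per arm the remaining bias was about 0.1 or less. If half of the dropouts have no week-13 score, about half of the bias remains.

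**5. Precision.** Suppose all 2.4 expected dropouts per arm have a week-13 score. The large-sample variance is then multiplied by 1 − r² × 2.4/24, which is 0.975 at r = 0.5 and 0.951 at r = 0.7, a gain of 2% to 5%. The effective n is 22.2 to 22.7 and power 83.8% to 84.9%, against 82.7%. If fewer dropouts have the score, the gain falls towards zero.

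**6. Scale.** The standard error of the difference with 21 per arm is 13 × √(2/21) = 4.0. A bias of 0.5 to 1.5 points is about 0.12 to 0.37 standard errors, 4% to 12% of the 13-point target, and 5% to 15% of the 10-point margin.

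**The case against.** The article never says that the analysis is restricted to observed cases. The same regression can be run after multiple imputation, and handling of missing outcomes commonly sits in a statistical analysis plan, which is not shown. This stands: observed-case handling is an inference from the model as written. Baseline-adjusted regression at the endpoint's own time point is also an accepted primary analysis.

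A reader might go further and infer a departure from intention-to-treat. The document does not support that. Failures and re-surgeries stay in, an intention-to-treat set is named, and a 10% sample-size allowance does not define an analysis population. The exclusion of patients without a repairable, proximal rupture is a separate question.

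A reader might also infer a loss of planned power. Steps 1 and 2 show that there is none.

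A further objection is that promoting the full mixed model over weeks 13, 26, 52 and 104 would cost too much. An unstructured covariance over four visits has 10 parameters for about 48 patients, in a plan that deliberately keeps its models small. It would also make the 6-month result depend on two-year data. This stands too, and it limits the remedy to weeks 13 and 26.

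What the objections do not remove is that the stated primary model makes no use of a scheduled early IKDC, and that no planned sensitivity set covers a missing 6-month score.

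**Conclusion.** The point holds as a modest improvement to a stated model. Run as written and without imputation, the primary regression leaves out about 2.4 of 24 patients per arm at the expected dropout and makes no use of their week-13 IKDC.

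The possible bias is roughly 0.5 to 1.5 points, well under half a standard error. It needs dropout that depends on early recovery differently in the two arms; with equal rates and the same mechanism it is zero. The size rests on an assumed correlation of 0.5 to 0.7, SD 13 and assumed dropout patterns, none of which the document gives except the SD (there for the change score). Bias above 1.5 points needs opposite patterns at the top of that range or more lopsided dropout than the plan gives reason to expect.

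**What to change.** State one of the following as the primary analysis for each comparison.

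- **Two-visit mixed model.** IKDC at weeks 13 and 26, with categorical visit, treatment-by-visit, baseline IKDC-by-visit, unstructured 2×2 covariance and Kenward-Roger degrees of freedom. The primary estimate is the week-26 treatment contrast. With no missing scores this reproduces the planned regression estimate exactly; I confirmed this on a simulated complete data set.
- **Planned regression after multiple imputation.** Impute the missing 6-month IKDC from the week-13 IKDC, baseline IKDC and treatment. This serves the same purpose and keeps the current model.

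In the DIS versus reconstruction comparison, keep the planned confounder adjustment in either version. Retain the regression on observed cases as a sensitivity analysis, and leave the longer mixed model as secondary.

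The cost is a change of wording and a slightly more complex model, with no new data and no change to 24 per arm. Both versions rely on missing-at-random and help little for patients lost before week 13, so report dropout by arm and timing with the result.

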### Randomization and blinding

Randomization will take place when the patient is diagnosed with an acute ACL rupture, which is MRI confirmed, fits all the in- and exclusion criteria (expect for the two inclusion criteria which are intra-operatively confirmed: proximal and repairable ACL rupture), and when the patient has signed the informed consent. The randomization procedure will be generated in Castor Electronic Data Capture software (Castor EDC, Amsterdam, the Netherlands). Castor uses stratified block randomization. Randomization will be stratified according to center. Per center a permuted block randomization with variable block size will be used.

The LIBRƎ study is a single-blind study meaning that the treating physicians (principal and sub-investigators) and the study coordinator are not blinded. The patient and the patient’s physiotherapist are blinded.

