In all the analyses there will be appropriately corrected for possible confounders (age, gender, working category, Tegner score of more than 7) especially in the analysis where the ACL reconstruction arm is compared to the DIS arm as this is a non-randomized comparison. As the sample size is small mainly ANCOVA models where only one covariate is added will be explored. As the sample size will not allow to combine all covariates in the model any conclusion for the non-randomized comparison will be carefully stated.

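### Randomisation is stratified by centre, but centre is not a term in the stated primary models; if centre predicts 6-month IKDC, the two randomised comparisons are conservative and give up some power.

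*Protocol article*

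**What the plan says.** On allocation, the protocol article (Randomization and blinding) states: "Randomization will be stratified according to center". It adds: "Per center a permuted block randomization with variable block size will be used". Two hospitals take part, and the Sample size section expects each to supply half of the patients.

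On analysis (Analysis of the primary outcome), the same model is given for all three pairwise questions: a "linear regression model with IKDC at 6 months as outcome and treatment, and IKDC at baseline as predictors". For the two randomised comparisons it adds: "This linear regression model will allow correction for possible confounders like age, gender and working category". The third comparison, DIS versus reconstruction, is described as non-randomised and is to be corrected for the same kind of covariates.

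The closing paragraph of Analysis of the secondary outcomes extends correction to all analyses and names "possible confounders (age, gender, working category, Tegner score of more than 7" as the candidates. It then limits the number of terms: "As the sample size is small mainly ANCOVA models where only one covariate is added will be explored".

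Centre is not named as a term in any of these places.

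**The concern.** Blocking within centre makes the arms nearly equal in centre composition. A difference between the hospitals therefore contributes almost nothing to the true variability of the treatment estimate. A model without centre does not use this: the between-centre variation stays in the residual, and the standard error is calculated as if that variation could have fallen unevenly on the arms. The standard error is then too large, the confidence interval too wide and the test conservative.

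The stake is efficiency. Each study plans on 21 evaluable patients per arm at alpha 0.025, with little to spare above 80% power. The fallback non-inferiority assessment with a 10-point margin would also be made with an interval wider than it needs to be.

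The third comparison differs. DIS patients come from study 1 and reconstruction patients from study 2, so stratification within each study does not balance centre between these two groups.

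**Working it through.** **Inputs from the Sample size section.** Difference 13 points, SD 13 for the change score per arm, power 80%, dropout 10%, and a test "using an independent samples t-test in which alpha is 0.025". Sidedness is not stated; two-sided reproduces the stated number. **Assumed:** the size of the centre effect, which the article does not give.

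**1. The plan's own figure.** The exact noncentral-t calculation, two-sided alpha 0.025, gives 21 per arm with power 81.5%. Dropout: 21 / 0.9 = 23.3, rounded up to 24 per arm, 48 per study. The stated sample size reproduces.

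**2. Mechanism, for a 10-point gap added to a within-centre SD of 13.** With two equal centres, a gap g adds g²/4 to the residual variance.
- Residual SD without centre: √(169 + 100/4) = √194 = 13.93.
- Reported SE without centre: 13.93 × √(2/21) = 4.30. SE with centre: 13 × √(2/21) = 4.01. Simulation gave 4.29 and 3.99.
- The critical t of 2.33 (40 df) therefore acts like 2.33 × 13.93/13 = 2.50, a two-sided type I error of about 1.7% against the nominal 2.5%.

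**3. Power if 13 is the total SD** (centre variation already inside it). 20,000 simulated trials per cell: 48 randomised, 24 per centre, blocks of 2, 4 or 6 (sizes assumed), 42 analysed. Baseline IKDC was left out of both models because its correlation with the outcome is not given. A variance share r corresponds to a gap of 26√r.

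| Variance share (gap) | Type I error, without / with centre | Power, without / with centre | Power given up |
|---|---|---|---|
| 0% (0) | 2.4% / 2.5% | 81.0% / 80.8% | none |
| 2% (3.7) | 2.3% / 2.3% | 81.7% / 82.0% | 0.3 |
| 5% (5.8) | 2.2% / 2.5% | 82.0% / 83.4% | 1.4 |
| 10% (8.2) | 1.8% / 2.3% | 82.0% / 85.2% | 3 |
| 20% (11.6) | 1.4% / 2.5% | 82.8% / 89.2% | 6 |

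A 10-point gap is a share of 25/169 = 15%. Simulated directly, it gave 82.7% without centre and 87.4% with it.

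**4. Power if 13 is the within-centre SD** (the gap comes on top).
- 3-point gap: 80.8% without centre, 81.1% with.
- 5-point gap: 80.2% without, 81.2% with.
- 10-point gap: 76% without, 81% with; a second run gave 77% and 82%.
- 13-point gap: 73% without, 81% with.

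**5. Non-randomised comparison.** The possible bias is the gap times the difference in centre proportions between the two groups. For illustration only: mixes of 60/40 and 40/60 with a 10-point gap give (0.6 − 0.4) × 10 = 2 points, in either direction. The article gives neither the mix by study nor the gap.

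**The case against.** The strongest reply concerns size. A reader might infer that leaving centre out takes the trial below its planned 80% power. The article does not support that. It plans on an SD of 13 per arm with an unadjusted t-test, and on the plain reading that SD already contains any centre variation. The unadjusted test then keeps at least 80% in every scenario in step 3, and adjustment is a gain above plan. A shortfall appears only when a large gap is added on top of 13. The Sample size section says only that the SD came from a pilot study, so that reading is possible but not established.

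A gap of 10 to 13 points is also large: 13 is the trial's own target difference, and the hospitals use similar surgical protocols and one rehabilitation protocol for all arms. At gaps of 3 to 5 points the loss is about 1 percentage point or less. This stands and limits the point.

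A second reply is that the article condenses a fuller plan, and that the covariate list for the primary models is open-ended, so centre might be added there. It is true that the article does not rule centre out. However, it writes out the model terms, names the candidates for all analyses without centre, and prefers one added covariate at a time. Centre would then have to compete with four named confounders, although it belongs in the model as part of the design.

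A third reply is that the DIS versus reconstruction comparison is already labelled non-randomised, with confounder correction and cautious conclusions promised. That is fair. Confounding by centre there is a possibility whose size the article does not allow anyone to state.

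**Conclusion.** The point holds as a matter of efficiency. The stated models omit the one factor on which randomisation is stratified. If centre predicts 6-month IKDC, the DIS versus IBLA and IBLA versus reconstruction tests are conservative and lose power: about 0 percentage points when centre explains 2% of variance or less, about 1 point at a 5-point gap, and 4 to 5 points at a 10-point gap. With no centre effect, including centre costs practically nothing.

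Power below 80% requires both that 13 is a within-centre SD and that the gap is large. Nor should a reader infer that the randomised results would be biased or the tests invalid: the estimates remain unbiased and the type I error errs on the safe side. For DIS versus reconstruction, unequal centre mix between the studies could bias the estimate in either direction, by an amount the article does not give.

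The figures assume two equal centres, 42 analysed patients per study, two-sided alpha 0.025, no baseline adjustment in either model, and an assumed centre effect.

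**What to change.** Add centre as a two-level fixed effect to all three primary models. State that it is a design term, always present and separate from the exploration of confounders one at a time, so that it does not use up the single covariate place. Carry it into the secondary regression models where feasible. Beside the sample size, it would help to say whether the SD of 13 is a total or a within-centre figure.

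The cost is one model term and one degree of freedom. No change to recruitment, randomisation or data collection is needed, and the change can be fixed before the data are analysed.

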### Study design

The **LIBRƎ** trial is a single-blind, multi-center, prospective, RCT comparing **L**igamys® anterior cruciate ligament (ACL) repair, ***I****nternal***B**race™ ACL repair and conventional ACL **re**construction for relative clinical efficacy and economic benefit.

Patients admitted for an acute traumatic knee sprain needing ACL surgery will be recruited at the Antwerp University Hospital and University Hospital Brussels, Belgium between February 2018 and June 2020.

The LIBRƎ study is single-blind, meaning that the patient and the physiotherapist are blinded to the performed surgical technique, but they are aware in which part of the study the patient participates (study 1 or study 2). Patient’s physiotherapist will follow a study-specific rehabilitation protocol (identical for the three treatment arms), depending on the readiness of the patient for a next phase and not restricted to a predefined time line.

In the study design, the time-dependent nature of ACL repair surgeries has been taken into account. The company Mathys Ltd. advices DIS to be performed within 3 weeks after the ACL rupture. Previous ACL repair surgery experience from the authors ([name]) led to a prolonged DIS ACL repair period within 4 weeks post-rupture. IBLA can be performed up to 12 weeks after the ACL rupture. ACL reconstruction is preferably performed when the knee has regained its function. This is commonly after 4 weeks post-rupture and can be performed up to many years later. Taken into account these time limits there will be two parallel studies (flowchart, Fig. 1):
Study 1 (RCT 1) with a time frame 0–4 weeks post-rupture: patients are randomized 1:1 to DIS or IBLAStudy 2 (RCT 2) with a time frame 5–12 weeks post-rupture: patients are randomized 1:1 to IBLA or conventional ACL reconstruction.

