#### Exploratory analyses

The IBLA arm (0–4 weeks) will be compared to the IBLA arm (5–12 weeks) to assess the optimal time frame for surgery.To identify if the patients that are intra-operatively confirmed of having an unrepairable and/or non-proximal, primary ACL rupture have certain characteristics in common and as such are an identifiable sub-population.

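### DIS versus reconstruction compares arms with non-overlapping surgery windows, so technique is fully confounded with time window and study; report it as estimation only, with an IBLA-anchored estimate beside the direct one

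*Protocol article*

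**What the plan says.** Under Study design, patients in study 1 have surgery 0–4 weeks after rupture and are randomised to DIS or IBLA. Study 2 runs "with a time frame 5–12 weeks post-rupture: patients are randomized 1:1 to IBLA or conventional ACL reconstruction". The Primary objective lists DIS versus reconstruction among its three pairwise comparisons.

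Under Analysis of the primary outcome, the third question is answered as follows: "Results from study 1 and study 2 will be compared using a linear regression model with IKDC at 6 months as outcome and treatment", with baseline IKDC as the other predictor. The text continues: "As this is a non-randomized comparison this model will correct for possible confounders like age, gender and working category". The closing paragraph of Analysis of the secondary outcomes extends the list to "possible confounders (age, gender, working category, Tegner score of more than 7" and adds: "As the sample size is small mainly ANCOVA models where only one covariate is added will be explored". It then says that conclusions from the non-randomised comparison will be worded with care, because the sample is too small to combine all covariates. Neither study nor time since rupture is named as a model term.

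The two IBLA arms are set against each other only under Exploratory analyses: "The IBLA arm (0–4 weeks) will be compared to the IBLA arm (5–12 weeks) to assess the optimal time frame for surgery".

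Sample size claims its power "with 80% statistical power between any of the two treatment arms", at alpha 0.025, "alpha corrected for the fact that per study data set 2 tests will be performed".

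**The concern.** The two surgery windows do not overlap. Anything that differs between early and late patients (time to surgery, referral delay, selection into one study or the other) is credited in full to DIS or to reconstruction. The protocol itself takes timing seriously. Its Background suggests that timing may explain the shorter work absence after DIS reported in a cited study, and it plans an early-versus-late IBLA comparison. Yet the model for this question has no means of accounting for timing.

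This is one of three questions under the primary outcome, and the Discussion states a hypothesis that DIS outperforms reconstruction at 6 months. The non-inferiority fallback with its 10-point margin is written for the arms in general and does not exclude this pair. A biased estimate could therefore support either a superiority or a non-inferiority statement.

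**Working it through.** **Inputs (Sample size):** difference 13 IKDC points, SD 13, alpha 0.025, power 80%, 21 evaluable and 24 randomised per arm. Sidedness is not stated. Two-sided is assumed because it reproduces the plan's figure.

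**1. The plan's own figure.** Two-sample t-test, noncentral t, two-sided 0.025: n = 20 per arm gives power 79.3% and n = 21 gives 81.5%. So 21 is the smallest adequate size, and 21/0.9 = 23.3 rounds up to 24. The stated numbers reproduce.

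**2. Can covariates separate technique from window?** With DIS and reconstruction patients only, the window (or study) indicator is identical to the technique indicator. A design matrix with intercept, technique and study has rank 2 of 3, so the study effect cannot be estimated alongside technique, whatever other covariates are added and however many patients are enrolled. With all four arms, the matrix for intercept, DIS, IBLA and study has rank 4 of 4. The IBLA arms supply the missing information. Adding the IBLA arms without a study term does not help: in simulation (4,000 runs, 21 per arm, no true difference, window effect 5 points) that model was biased by 5.0 points, exactly like the direct comparison.

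**3. Size of the bias problem.** The documents give no window effect, so values are assumed. The direct SE is 13 × √(2/21) = 4.01. With no true difference between techniques, the two-sided 0.025 test (40 df) rejects as follows:

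| Assumed early–late difference | False-positive rate, direct comparison |
|---|---|
| 0 | 2.5% |
| 3 points | 6.6% |
| 5 points | 15.1% |
| 8 points | 37.8% |

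**4. The anchored contrast.** (DIS − IBLA in study 1) + (IBLA − reconstruction in study 2) has SE 13 × √(4/21) = 5.67, with 4 × 21 − 4 = 80 df.

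| | Direct | Anchored |
|---|---|---|
| SE | 4.01 | 5.67 |
| Power for 13 points, two-sided 0.025 | 81.5% | 50.6% |
| 97.5% CI half-width | 2.329 × 4.01 = 9.3 | 2.284 × 5.67 = 13.0 |

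Eighty per cent power for the anchored contrast would need 39 evaluable patients per arm, or 39/0.9 = 43.3, rounded up to 44 randomised.

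**5. Stress test of the anchored contrast.** It removes a window effect common to all techniques, but not one that differs by technique. With an assumed technique-by-timing interaction of 3, 5 or 8 points, its false-positive rate is 4.6%, 8.6% or 19.7%. It is less exposed than the direct comparison at the same bias, partly because its SE is larger, but it is not immune.

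These calculations omit baseline IKDC. Adjusting for it may shorten both intervals.

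**The case against.** **The limitation is disclosed.** The comparison is labelled non-randomised, restraint is promised, and the Discussion explains at length why reconstruction was not placed in study 1. This stands, and a reader should not infer that the protocol presents the comparison as equal to the randomised ones. But the stated ground for caution is sample size, and step 2 shows that sample size is not the obstacle.

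**The covariate list is open and the full model may be elsewhere.** True, but with only these two arms no added covariate can separate technique from window. The stated comparison is at fault, not a missing detail.

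**Anchoring has its own assumption.** This also stands. The Background links success of repair to acute, proximal ruptures with better healing capacity, while reconstruction removes the ligament, so a timing effect specific to repair is conceivable. DIS and reconstruction each occur in one window only, so the assumption cannot be tested. It is tempting to call the anchored contrast a fully protected replacement test at 2.5%; step 5 shows why the design does not support that.

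**The direct contrast may be the practical question:** early DIS against later reconstruction, each at its usual time. That is a legitimate reading of the contrast, but the Primary objective speaks of techniques, and early and late presenters may differ in other ways too.

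**Multiplicity.** A reader might infer that three primary tests at 0.025 break the 5% level. The documents do not support this as a fault. The 0.025 is explained by two tests per study data set, and DIS versus reconstruction is already one of the two in each. The error within each data set is about 4.6%.

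**Conclusion.** The point holds in this form: as a comparison of techniques, the direct DIS versus reconstruction analysis is completely confounded with time window and study, and neither the listed covariates nor a larger sample can cure it. The rank argument needs no numerical assumption. The false-positive rates of 6.6%, 15.1% and 37.8% rest on assumed differences of 3, 5 and 8 points and are illustrative.

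The IBLA arms allow a better-founded estimate that the plan does not use. With SD 13, 21 per arm and two-sided alpha 0.025, that estimate has about 51% power. Its 97.5% half-width of 13.0 points exceeds the 10-point margin, so at that confidence level non-inferiority could not be shown even with an observed difference of zero. It therefore belongs in the report as an estimate with its assumption stated, not as a confirmatory test. The power claim for any two arms holds for this pair only if the confounding is ignored.

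**What to change.** - **Analysis of the primary outcome, third question:** fit one regression on all four arms with 6-month IKDC as outcome and technique, study, baseline IKDC and centre as terms. Report the IBLA-anchored DIS versus reconstruction estimate with its confidence interval, next to the direct adjusted comparison.
- **Assumption:** state that anchoring requires the technique effect not to depend on timing, and that this design cannot test it.
- **Claims:** treat DIS versus reconstruction as estimation only. Make no superiority claim, and no claim against the 10-point non-inferiority margin from the direct comparison.
- **Reason for caution:** name the confounding with time window and study, not only the small sample.
- **Sample size:** limit the 80% power statement to DIS versus IBLA in study 1 and IBLA versus reconstruction in study 2, and give about 51% for the anchored contrast.

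The cost is analysis wording, a restated power figure and a wider interval (half-width about 13.0 instead of 9.3 points). No new patients or visits are needed. A confirmatory anchored comparison at 80% power would be a different matter, at 44 randomised per arm instead of 24, and would still rest on the untestable assumption.
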